If we observe significant treatment effects (e.g., reduced adverse events) from the performance coaching intervention, we will conduct follow-up analyses to strengthen causal inference. Drawing on methods from treatment mechanism research, we will test whether hypothesized mediators (e.g., person-centered care, retention in treatment) are associated with outcomes. We will also examine moderation by population characteristics and regional variation (e.g., gender, location), as well as provider-level differences in implementation. Lagged treatment effects will be assessed using interaction terms between treatment and time since intervention start by cohort. These exploratory analyses will inform interpretation and guide qualitative inquiry.

*Data and specification:*

We will join multiple administrative data sources from New York State for years 2021–2027 to form our analytical dataset. We will use Client Data System (CDS), Medicaid claims, and NYS vital statistics data to form the analytic dataset. The OASAS treatment registry (CDS) will provide extensive clinical data on clients at treatment admission and will include descriptions of providers through the provider data system (PDS). Medicaid will provide medical diagnoses, healthcare services, SUD treatment services, and medication utilization data. The New York State Vital Statistics will be received from the outpatient clinics in the form of all-cause mortality for clients participating in the trial. Additional OASAS data will provide operational and staffing information for each clinic. To date, 75% of clients in the OASAS registry have been linked to Medicaid claims data.

Quality measures from Project 1 will encompass patient, clinic, and organizational factors, including demographics, clinical complexity, substance use patterns, prior healthcare utilization, community access, substance use trends, resources, psychosocial interventions, clinic structure, staffing, and MOUD use and retention. Primary outcomes include adverse events, healthcare utilization, and mortality. Adverse events are defined as SUD-related hospitalizations or emergency department visits, including overdose, within 12 months of treatment entry. Healthcare utilization includes all-cause emergency department visits or hospitalizations within the same timeframe. Mortality will be assessed as all-cause mortality. Outcome variables will be risk-adjusted to account for client health status.

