*Statistical Analyses of the Proposed Stepped-Wedge Trial:* Analyses will begin with examination variable distributions, appropriate transformations, and patterns for, followed by formal imputation methods if needed [110–112]. We will use Generalized Linear Mixed Models (GLMM) for the stepped-wedge design [106].

*Power Analysis for Primary Outcome Statistical power:* Power estimation for specific outcomes was conducted using PASS 2022 software and Monte Carlo simulation [113]. Sample size and baseline rates (μ) were estimated using administrative data. For 80% power, α = 0.05, ICC = 0.05, and a 5-crossover-point stepped-wedge-RCT with 7 clinics starting at each point, power calculations indicate 80% power to detect a small decrease (RR = 0.93) in adverse events with 35 clinics and 350 clients per clinic per 6-month period (n ≈ 73,500 total observations). This corresponds to a decrease from 0.23 to 0.21 events per 6 months. In racial/ethnic subgroups (10% of clients, n ≈ 35 per site), power remains 80% to detect a modest decrease (OR=0.78), from 0.23 to 0.18.

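### Moderation analyses appear conditional on a significant treatment effect, while 80% power in racial/ethnic subgroups is stated without that condition; if the condition applies, a benefit confined to a 10% subgroup would usually go unexamined.

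*Protocol article*

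**What the plan says.** Two neighbouring parts of the Protocol article (Data and analytic plans, Project 3: Stepped-wedge trial) bear on this.

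The paragraph on follow-up analyses begins "If we observe significant treatment effects (e.g., reduced adverse events) from the performance coaching intervention, we will conduct follow-up analyses". Mediation comes next, then "We will also examine moderation by population characteristics and regional variation". Its examples are gender and location, and the same sentence adds provider-level differences. Lagged effects follow. The paragraph closes "These exploratory analyses will inform interpretation and guide qualitative inquiry", which gives the whole set one status.

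The power paragraph sets the design as "For 80% power, α = 0.05, ICC = 0.05, and a 5-crossover-point stepped-wedge-RCT with 7 clinics starting at each point". Its overall claim is "80% power to detect a small decrease (RR = 0.93) in adverse events". The sample behind that claim is "35 clinics and 350 clients per clinic per 6-month period (n ≈ 73,500 total observations". For racial/ethnic subgroups (10% of clients, about 35 per site) it adds "power remains 80% to detect a modest decrease", given as OR 0.78 and as 0.23 to 0.18. No condition is attached. The article describes no other subgroup analysis of the trial outcome.

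**The concern.** On its natural reading, the opening condition governs everything in the follow-up paragraph, including moderation by population characteristics, and race/ethnicity is such a characteristic. The only quantitative route to a racial/ethnic effect that the article describes then opens after a significant treatment effect. The power statement reads as if the subgroup test were always run.

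The difference matters most when the benefit is concentrated in a small group. A large effect in 10% of clients barely moves the overall rate, so the overall test will usually miss it and the subgroup analysis would not be run. The Introduction motivates the study by worse care and outcomes in Black and Latinx clients, so this is a case the team would want to see. If the team ran the analysis anyway after a null overall result, it would depart from the published text and look post hoc.

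**Working it through.** **Inputs from the power paragraph.** 35 clinics, 5 crossover points with 7 clinics each, 350 clients per clinic-period (35 in the subgroup), ICC 0.05, α 0.05, baseline rate 0.23. Two-sided testing is assumed, since the article does not say. The number of periods follows from the stated total: 73,500 / (35 × 350) = 6. The trial description elsewhere has six cohorts and seven periods; the check uses the design that was powered.

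**Stated powers.** I used a cross-sectional stepped-wedge variance (Hussey-Hughes, generalised least squares) with total variance p(1 − p).
- Overall, RR 0.93 (0.23 × 0.93 = 0.2139, a drop of 0.0161): 85.6% with a constant clinic effect (cluster autocorrelation 1) and 79.4% with autocorrelation 0.99.
- Subgroup, 0.23 to 0.18: 87.8%. Subgroup, OR 0.78 (0.23 to 0.189): 72.8%. The two labels are not the same effect: 0.18/0.23 is a risk ratio of 0.78, and the odds ratio is 0.73.

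The stated 80% lies between the two subgroup results. The autocorrelation used in the power software is not given, so I do not call the figure wrong.

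**Dilution.** If 10% of clients fall from 0.23 to 0.18 and the rest do not change, the overall drop is 0.10 × 0.05 = 0.005, from 0.23 to 0.225 (RR 0.978).

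**Chance that the overall test is significant, from the plan's own power.** No variance model is needed here.
- SE implied by 80% power at a drop of 0.0161: 0.0161 / (1.960 + 0.842) = 0.00575.
- z = 0.005 / 0.00575 = 0.87.
- Probability = Φ(0.87 − 1.96) + Φ(−0.87 − 1.96) ≈ 0.14.
- With the rounded drop of 0.02 (0.23 to 0.21): SE = 0.02 / 2.802 = 0.00714, z = 0.70, probability ≈ 0.11.

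**The same chance from the variance model, by share of clients who benefit (drop of 0.05, none in the others).**

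| Share benefiting | 35 clinics, autocorrelation 1 | 35 clinics, autocorrelation 0.95 |
|---|---|---|
| 10% | 15% | 10% |
| 20% | 46% | 27% |
| 30% | 79% | 52% |
| 50% | 99.6% | 92% |

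Power for a conditional subgroup test cannot exceed these figures. At a 10% share, both tests are significant in 14.5% (autocorrelation 1) or 10% (0.95) of trials, against 88% or 85% for the subgroup test run unconditionally.

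**Adding TAU clinics.** The analysis section says the model will be expanded with these clinics. I assumed 550 − 35 = 515 clinics, a TAU indicator and shared period effects, with 80 to 350 clients per clinic-period. The lower value comes from 91,000 / 571 ≈ 159 per year, about 80 per half-year. At a 10% share the overall test is significant in 27-30% of trials (autocorrelation 1) or 17-18% (0.95). At a 20% share the figures are 77-82% and 52-54%.

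**If all clients benefit equally by 0.05,** z is 0.05 / 0.00575 = 8.7. The condition is always met and costs nothing.

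**The case against.** The condition on the racial/ethnic analysis is inferred. The follow-up paragraph gives gender and location as its examples and does not name race/ethnicity. The power paragraph concerns an effect within a subgroup, whereas moderation is a difference in effect between groups. One could read the former as planned and powered, and the latter as exploratory work after a positive result. The condition also speaks of effects in the plural and by example, so a significant result on healthcare utilization, mortality or retention might satisfy it. All of this stands, and it makes the point conditional. It does not remove the mismatch, because the article describes no unconditional analysis to which the subgroup power could belong.

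A condensed article may leave the subgroup model to a statistical analysis plan. That is accepted: the point is not that a model is missing, but that two statements the article does make pull apart.

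The scenario is extreme. Coaching is delivered to clinic leadership and staff, nothing in the article predicts an effect confined to one group, and two benefiting groups of 10% each would already double the share. The TAU clinics also raise the chance of a significant overall test, though less so if the planned TAU-by-time term absorbs the shared trend. These points limit the size of the loss, but at a 10% share it remains large.

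Looking at moderation only after a positive main result is a recognised guard against false-positive subgroup claims. That is a fair reason for caution in labelling. It does not explain why a subgroup analysis was sized without mention of the condition.

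**Conclusion.** The two paragraphs need to be reconciled. If the racial/ethnic analysis sits under the condition, and a fall from 0.23 to 0.18 is confined to 10% of clients, the adverse-event test would be significant in about 10-15% of trials with the 35 clinics, or roughly 17-30% with TAU clinics sharing the period effects under the assumptions above. The stated 80% would then not be delivered. This rests on adverse events alone opening the condition and on no benefit in other clients. The loss falls quickly as the share grows and is negligible if all clients benefit.

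A reader might infer that the plan's true subgroup power is about 12%, or that the plan certainly suppresses the racial/ethnic analysis. The documents support neither. The first holds only in one extreme scenario with the 35 clinics alone, and the second depends on reading race/ethnicity into a clause that does not name it. Nor is the 80% itself shown to be wrong for a test that is run unconditionally. The primary test, its estimate and its error rate are unaffected.

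**What to change.** In the follow-up paragraph, take the racial/ethnic analysis out of the conditional clause. State that the coaching-by-race/ethnicity interaction and the subgroup-specific effects will be reported with confidence intervals whatever the overall result, labelled secondary or exploratory. Mediation can stay conditional. If the team always meant to run this analysis unconditionally, one sentence saying so is enough. If it does mean to keep the condition, the power paragraph should say that the 80% does not allow for it.

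The cost is wording and one extra model on data already being collected, with no change to design or sample size. The downside is one more analysis to label for multiplicity.

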We will initiate a stepped wedge randomized controlled trial involving 1) 35 clinics receiving a performance coaching intervention and 2) a treatment as usual (TAU) condition for all clinics not participating in the intervention. Additionally, qualitative interviews with stakeholders and surveys of all 550 outpatient clinics will be conducted at three different points in time (years 1, 3, and 4). We will use administrative data from 2021–2027, including records from the Office of Addiction Services and Supports (OASAS) treatment registry, Medicaid, and vital statistics, to monitor client outcomes. This concurrent mixed-methods study [94] will evaluate the impact of the OASAS QM2 strategy on patient outcomes and statewide stakeholders, focusing on retention in care and adverse events (emergency department visits, hospitalizations, and mortality). Clinics will be randomized to one of five sequences, varying the timing of the intervention between years 2 and 4.

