Before the trial begins, clinics receiving the QM2 intervention will be randomized into six cohorts of six-month long interventions over three years. Clinics are randomized to onset of intervention in one of six time periods over the three years of the intervention rollout (years 2–4 of the project) and tracked using administrative data. Administrative data will be used for all clinic clients during each of the seven six-month periods (n ≈ 350/clinic) will be drawn from administrative data. The first six-month period will be a baseline prior to any intervention. Six clinics will be assigned randomly to one of six time periods for onset of intervention. Using administrative data, we will track clients within each clinic over four years, including a pre-intervention six-month baseline period. During the same four-year period, clients in clinics not participating in the stepped-wedge trial will be tracked to better understand changes in outcomes under treatment as usual (TAU) and to compare the outcomes of those clinics with clinics receiving the quality management intervention. We anticipate a final study population of approximately 91,000 individuals per year who are receiving treatment from one of the 571 enrolled outpatient substance use treatment programs. Because this is a stepped-wedge trial, all clinics (and as a result all clients within the clinics) will eventually get the intervention, the randomization will have to do with when the clinic is randomized rather than being assigned to a control or intervention group. Fig 2 illustrates the structure of the stepped-wedge trial.

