### Data and analytic plans

#### Project 3: Stepped-wedge trial.

*Quantitative Methods:* We will utilize Generalized Linear Mixed Models (GLMMs), which are commonly applied in the analysis of stepped-wedge trial [106,107]. The models will be structured as follows:

$$F(\mu_{ijk})=\mu +\beta_{j}+{\delta X}_{ij}+\alpha_{i}+\phi_{ik},\;\alpha_{i}\sim N\left(\text{0},\tau_{\alpha }^{\text{2}}\right),\;\gamma_{ij}\sim N(\text{0},\tau_{\phi }^{\text{2}})$$

where $\beta_{j}$ represents a fixed effect for time, $X_{ij}$ is an indicator for intervention in clinic *i* at time *j* (coded 0 for the control condition, then 1 from the start of the intervention in the clinic until the end of the study), and δ denotes the intervention effect. The models include random effects to account for clustering at both the clinic and individual patient levels, which are assumed to follow a normal distribution with mean zero and variances $\tau_{\alpha }^{\text{2}}$ and $\tau_{\phi }^{\text{2}}$, respectively. We will estimate the intervention effect while controlling for secular trends and adjusting for clustering within clinics ($\alpha_{i}$) and individual ($\phi_{ik}$), using mixed effects modeling with a binary distribution and logit link function. The models will be fitted using the *glmmTMB* package in R software [108,109]. The primary outcome will be adverse events, and the fixed-effects coefficients for the intervention effect, exponentiated, will indicate the extent to which the intervention changes the rate of adverse events. An offset term can be included to capture client differences in time at risk due to timing of treatment entry.

TAU clinics will be included in the model with an indicator variable. A post-hoc test of the intervention effect coefficient will compare TAU and performance coaching, and a TAU-by-time interaction will assess time trends within the TAU group. The GLMM analysis will be expanded by adding the clinics not receiving the performance coaching intervention during the study period. For TAU clinics, the intervention indicator will be coded 0 in all periods. This provides an additional estimate of trends ($\beta_{j}$) in outcomes in a much larger sample of clinics. Because the fixed effect for time ($\beta_{j}$) is estimated, the intervention effect (δ) can be interpreted as the degree to which performance coaching results in a lower rate of adverse events than what would be expected due to time alone in the absence of intervention.

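### The one sentence on how deaths reach the study contradicts the rest of the protocol on source and coverage; read literally, it rules out the treatment-as-usual comparison for mortality

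*Protocol article*

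**What the plan says.** All references are to the protocol article.

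- **Route and population of death data** (Data and specification, under Project 3: Stepped-wedge trial). State vital statistics will be "received from the outpatient clinics in the form of all-cause mortality for clients participating in the trial". No other sentence says both how deaths arrive and for whom.
- **Source, same paragraph.** The opening lines describe a join of New York State administrative sources: "We will use Client Data System (CDS), Medicaid claims, and NYS vital statistics data to form the analytic dataset".
- **Source, Introduction (last paragraph).** The administrative records for 2021–2027 are the "treatment registry, Medicaid, and vital statistics, to monitor client outcomes".
- **Coverage, Materials and methods (Project 3 aims).** Over the same four years, "clients in clinics not participating in the stepped-wedge trial will be tracked to better understand changes in outcomes under treatment as usual (TAU"), and their outcomes are to be compared with those of coached clinics.
- **Coverage, Quantitative Methods.** "TAU clinics will be included in the model with an indicator variable", with the intervention term at zero throughout.
- **Status of mortality.** Data and specification states: "Primary outcomes include adverse events, healthcare utilization, and mortality". It adds: "Mortality will be assessed as all-cause mortality". The Abstract also counts mortality among the primary clinic outcomes, within 12 months of admission. Quantitative Methods says only: "The primary outcome will be adverse events".

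**The concern.** A listed primary outcome needs one stated source and one stated population. Here the sentence that supplies both disagrees with the rest of the plan on each.

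On **coverage**, the analysis adds TAU clinics to the model to estimate time trends in a much larger sample and to compare those clinics with coaching. If deaths are held only for clients of the coached clinics, neither can be done for mortality.

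On **source**, a central state file finds deaths in the same way whatever a clinic's coaching status. A route through clinics that know when they are being coached gives no such guarantee. If capture shifted when a clinic crossed over, the mixed model would attribute the shift to the intervention. The fixed time effects would not absorb it, because it would follow each clinic's own crossover and not calendar time.

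**Working it through.** The article gives no mortality rate, sample size or power, so there is no stated figure to reproduce. The check compares statements, followed by two short calculations.

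**1. Source.** One phrase says the data arrive from the outpatient clinics. Against it stand the opening of the same paragraph and the Introduction, both of which treat vital statistics as a state source joined with the registry and Medicaid. These cannot all describe the same data flow.

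**2. Coverage.** The answer depends on what it means to participate in the trial, and the article uses the term in two ways:

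- The Abstract and the Project 3 design text describe TAU clinics as ones outside the trial. Under that usage, the mortality sentence excludes TAU clients.
- The Introduction and the Project 3 aims heading call TAU one of the trial's two conditions. Under that usage, TAU clients could be included.

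The plan to track and model TAU outcomes fits only the second usage.

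**3. Programs without mortality data under the first usage.** Inputs: 35 coached clinics; 571 programs (Project 3 design text) or 550 (Introduction and Component 2).

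- 571 − 35 = 536; 536/571 = 93.9%
- 550 − 35 = 515; 515/550 = 93.6%

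**4. Possible bias if clinics were themselves the source of deaths.** Let s0 be the share of deaths captured in control periods and s1 the share captured under coaching. Then

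observed RR = true RR × (s1/s0).

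The article gives no capture rates, so the range is an assumption: each share lies between 70% and 100%. With a true RR of 1.00:

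| s0 | s1 | observed RR |
|---|---|---|
| 100% | 70% | 0.70 |
| 90% | 80% | 0.89 |
| equal | equal | 1.00 |
| 80% | 90% | 1.13 |
| 70% | 100% | 1.43 |

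The range runs both ways and follows entirely from the assumed shares. It shows that the source matters; it is not an estimate of bias in this trial.

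**The case against.** The strongest reply is that this is a drafting slip. The grammatical subject of the sentence is New York State Vital Statistics, not deaths reported by clinics, and the surrounding text treats these as linked state records. The phrase may have been meant to say that the records concern clients of the outpatient clinics. Even taken literally, it may describe only who passes the records on. This stands, and the ascertainment concern is therefore conditional.

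Second, since parts of the article call TAU a condition of the trial, its clients may be covered after all. This also stands as a possible reading. It does not remove the conflict, because the Abstract and the design text use the opposite sense.

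Third, Quantitative Methods names only adverse events as primary, the power calculation addresses only those, and the randomised comparison within the wedge does not need TAU deaths. All true, and this limits the damage. Mortality is nevertheless listed as primary in two places, and the Introduction counts it among the adverse events.

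A reader might go further and infer that coached clinics will decide which deaths are counted, and that better record keeping under coaching will push the result towards apparent harm. The documents do not support that. They nowhere say that clinics determine deaths, they give no capture rates, and the coaching content they describe does not mention death ascertainment. The same 35 clinics also supply the control periods before crossover, so bias within the wedge requires capture to change with coaching.

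**Conclusion.** The protocol contradicts itself on the source and coverage of a listed primary outcome, and the passages should be reconciled.

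- **Coverage.** If the sentence is literal and TAU lies outside the trial, about 94% of programs (536 of 571, or 515 of 550) have no mortality data and the TAU comparison of mortality cannot be made. If TAU counts as part of the trial, this loss does not follow.
- **Ascertainment.** If clinics are literally the source, capture could change with coaching and bias the effect. Direction and size cannot be known from the documents. There is no such bias if capture is equal or if state records are used.

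It would be too strong to conclude that mortality has been removed from the TAU clinics, or that ascertainment has been handed to the coached ones; both depend on one disputed reading. Even on the mildest reading, the sentence misstates where a primary outcome comes from. It should be corrected before the data are assembled.

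**What to change.** Replace the sentence in Data and specification with one to this effect: all-cause deaths are taken from the New York State vital statistics file, linked centrally to the treatment registry, for all clients of coached and TAU clinics, over the same window from admission. The Abstract already gives 12 months for that window.

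The article should also use one meaning of trial participation throughout, so that the status of TAU clients is clear.

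The cost is mainly wording, because the state file and its joining to the registry are already planned. The article mentions data-use agreements with the state agency but does not show their terms, so the sponsor may need to confirm that they cover death records for TAU clients.

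### The primary outcome is visible only in Medicaid claims, linked so far for 75% of registry clients, but the trial is powered on all 350 clients per clinic-period

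*Protocol article*

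**What the plan says.** In the protocol article, under Data and analytic plans (Project 3: Stepped-wedge trial), the primary endpoint is named: "The primary outcome will be adverse events". The data specification in the same section defines it: "Adverse events are defined as SUD-related hospitalizations or emergency department visits, including overdose, within 12 months of treatment entry".

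That specification names three client-level sources. The treatment registry supplies clinical information at admission, and vital statistics supply all-cause mortality. For the third source it says: "Medicaid will provide medical diagnoses, healthcare services, SUD treatment services, and medication utilization data". On coverage it adds: "To date, 75% of clients in the OASAS registry have been linked to Medicaid claims data".

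Under Materials and methods (Project 3 aims) the denominator is everyone: "Administrative data will be used for all clinic clients during each of the seven six-month periods", with n given as about 350 per clinic. The power analysis uses the same size, "350 clients per clinic per 6-month period", with 35 clinics and about 73,500 observations, for 80% power at a rate ratio (RR) of 0.93.

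The only exposure adjustment mentioned is optional: "An offset term can be included to capture client differences in time at risk due to timing of treatment entry". The only missing-data provision is formal imputation, if needed.

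**The concern.** Four statements do not fit together: the outcome is a claims outcome, claims are linked for three clients in four, the analysis counts every client, and the power calculation counts every client. A client with no linked claims has no observed primary outcome and adds no information on it.

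Two things are at stake. First, the stated 80% power at RR 0.93 rests on a sample larger than the one in which the outcome can be seen. Second, the population and the follow-up time for the primary outcome are left unclear. The article does not say that the claims outcomes describe linked clients only. The offset it mentions is driven by date of treatment entry, not by the time during which a claim could have appeared. If unlinked clients are mostly people outside Medicaid (an assumption), their outcomes are missing by design, and generic imputation cannot readily supply them.

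**Working it through.** **Inputs from the power analysis.** 35 clinics, five crossover points with 7 clinics each, 350 clients per clinic per six months, intraclass correlation 0.05, α = 0.05, baseline 0.23 events per six months, RR 0.93 (also given as 0.23 to 0.21), subgroup of about 35 per site (0.23 to 0.18). From the data specification: 75% linked.

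**Assumptions.** Two-sided test, random clinic intercept only, repeat observations treated as independent, and 75% applying equally to every trial clinic and period.

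**1. The plan's own count.** 35 × 350 × 6 = 73,500, exactly the stated total. It implies six periods and no allowance for unlinked clients. At 75%: 0.75 × 350 = 262.5 per clinic-period, and 0.75 × 73,500 = 55,125 observations.

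**2. Variance formula (Hussey and Hughes).** With I = 35 clinics, T = 6 periods and s² = σ²/m:

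Var(δ) = I·s²·(s² + T·τ²) / [(I·U − W)·s² + (U² + I·T·U − T·W − I·V)·τ²]

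For this layout U = 105, W = 2,695 and V = 385. The bracket terms are 35 × 105 − 2,695 = 980 and 11,025 + 22,050 − 16,170 − 13,475 = 3,430.

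**3. RR 0.93, binomial variance.** The rates are 0.23 and 0.2139, the difference is 0.0161 and the mean is 0.222. So σ² = 0.222 × 0.778 = 0.1727 and τ² = (0.05/0.95) × 0.1727 = 0.00909.

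- m = 350: s² = 0.000493, SE = 0.00548, 0.0161/0.00548 = 2.94, power = Φ(2.94 − 1.96) = 84%.
- m = 262.5: s² = 0.000658, SE = 0.00632, 0.0161/0.00632 = 2.55, power = Φ(2.55 − 1.96) = 72%.

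**4. RR 0.93, Poisson variance (σ² = 0.222).** The SE is 0.00621 with 350 and 0.00716 with 262.5, so power is 74% and 61%. The stated 80% lies between the two models' results with the full 350, so it is reproduced to within the choice of variance and the rounding of RR. If σ² is instead taken as 0.95 of the total variance, the figures are 85% to 74% (binomial) and 76% to 64% (Poisson), which is the same loss.

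**5. Starting from exactly 80%.** The SE grows by close to 1/√0.75 = 1.155. At the effect that has 80% power with 350, power becomes Φ(2.80 × √0.75 − 1.96) ≈ 68% under either variance model.

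**6. How much the detectable effect moves.** With binomial variance, the RR with 80% power goes from 0.933 to 0.923, a shift of about 0.01.

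**7. The absolute decrease as printed, 0.23 to 0.21** (RR 0.913). Binomial: SE 0.00630 with 262.5, power 89%. Poisson: SE 0.00713, power 80%.

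**8. Subgroup, 0.23 to 0.18.** The size becomes 0.75 × 35 = 26.25 per site. Binomial: SE 0.0164 to 0.0188, power 86% to 76%. Poisson: SE 0.0184 to 0.0211, power 78% to 66%.

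**9. Size needed to keep 350 linked clients.** 350/0.75 ≈ 467 clients per clinic-period.

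**The case against.** **350 may already be linked clients.** The power section says sample size and baseline rates came from administrative data, and a baseline event rate can be estimated only where events are observed. That is a fair point, and it leaves the reading of 350 open in that section. But the design section attaches the same figure to all clinic clients, so one of the two places needs correcting either way.

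**75% is not a trial parameter.** It describes the whole registry, to date. Linkage in the 35 clinics could be higher or lower and may improve. This stands: 262 is conditional on 75% applying.

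**The printed decrease is still well powered.** True, as step 7 shows. What is not delivered at 75% linkage is the statement at RR 0.93.

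**The treatment-as-usual clinics will add precision.** They may. Suppose 536 such clinics (571 − 35) with 80 clients per period (91,000/571/2), also cut by 25%, share the trial clinics' period effects. Power at RR 0.93 with 262.5 would then be about 96% (binomial) or 91% (Poisson). The article, however, also plans a treatment-as-usual-by-time interaction. Average exposure in the trial clinics rises in equal steps (0, 1/5, …, 1), so in the same model a linear interaction of that kind absorbs the extra information. The stated power also rests on the 35 clinics alone.

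**Coding rules belong in the analysis plan.** A reader might infer that unlinked or uncovered time will be counted as event-free, so that a change in coverage after coaching starts would look like a treatment effect. The article does not say this. It codes no such time as zero, the offset is only a possibility, imputation is mentioned, and the coaching content does not include benefit enrolment. Coverage changes common to all clinics would fall into the period effects.

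**Conclusion.** The concern holds as an inconsistency between the outcome source, the linkage figure and the sample size. If 75% linkage applies in the trial clinics and 350 means all clients, power at RR 0.93 falls by about 11 to 12 points and the stated 80% is not reached: it is roughly 68% from an exact 80% start, and 61% to 72% at RR 0.93 depending on the variance model. The subgroup statement loses about 10 to 12 points. The practical loss is moderate, because the detectable RR shifts by about 0.01 and a fall to 0.21 keeps about 80% to 89% power before any gain from the treatment-as-usual clinics.

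That Medicaid is the only source of the primary outcome is an inference from the list of sources, but no other listed source carries visits or admissions.

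Bias from a coverage change is a conditional risk, not a demonstrated fault. As illustration only: if uncovered time were coded event-free and coverage rose from 75% to 78% in coached periods (both assumptions), a null effect would appear as 0.78/0.75 = 1.04 and a true 0.93 as 0.93 × 1.04 = 0.967.

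**What to change.** - Define the analysis set for the emergency department and hospital outcomes as Medicaid-linked clients. Set time at risk to Medicaid-enrolled time after admission, not time since treatment entry alone, and state that unlinked or uncovered time is not counted as event-free.
- Restate overall and subgroup power with the linked number: about 262 and 26 per clinic-period at 75%, or the rate expected in the recruited clinics. If 350 already means linked clients, correct the design section instead and say so in the power section.
- Report linkage by clinic, period and coaching status, so that any shift in coverage can be seen.
- Keep all registry clients for mortality, which comes from vital statistics.

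The cost is wording and a slightly less favourable power figure. The real downside is that the claims outcomes then describe Medicaid-covered clients only, which should be stated as a limit on generalisation.
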